## Abstract

**Background:**

Simulation-based training in neonatal resuscitation is more effective when reinforced by both practice and continuous improvement processes. We aim to evaluate the effectiveness of a quality improvement program combined with an innovative provider feedback device on neonatal resuscitation practice and outcomes in a public referral hospital of Nepal.

**Methods:**

A pre- and post-intervention study will be implemented in Pokhara Academy of Health Sciences, a hospital with 8610 deliveries per year. The intervention package will include simulation-based training (Helping Babies Breathe) enhanced with a real-time feedback system (the NeoBeat newborn heart rate meter with the NeoNatalie Live manikin and upright newborn bag-mask with PEEP) accompanied by a quality improvement process. An independent research team will collect perinatal data and conduct stakeholder interviews.

**Discussion:**

This study will provide further information on the efficiency of neonatal resuscitation training and implementation in the context of new technologies and quality improvement processes.

**Trial registration:**

10.1186/ISRCTN18148368, date of registration-31 July 2018

## Background

Worldwide, approximately 10 million newborns every year require assistance to breathe after birth. Studies show that timely and effective ventilation of these babies can significantly improve newborn survival. However, insufficient number of providers trained in newborn resuscitation and a lack of clinical tools remain significant barriers [1–3]. The American Academy of Pediatrics (AAP) and their partners developed Helping Babies Breathe (HBB), a simulation-based curriculum, to train and equip healthcare providers to evaluate and support breathing at birth [4].

However, in resource-constrained environments like Nepal, there are several challenges to neonatal resuscitation training and implementation, including lack of time, equipment and resources [5]. Singhal et al., while developing an education program for newborn resuscitation in resource-constrained settings identified that additional training, education and guidance are necessary for improve retention and assimilation of resuscitation skills in clinical practice [6].

Simulation-based training has been used increasingly to help health workers convert knowledge and skills into practice [7, 8]. Simulations help workers combine and reinforce their academic, intellectual, practical and interactive skills [9]. However, not much is known about the translation of training into clinical practice [10]. Also, health workers in poorly resourced settings may be unfamiliar with simulation-based training or even how to meet their training needs [11]. We believe that regular simulation-based practice in the form of drills will help them to translate their knowledge and skills into practice.

The Rapid Feedback for quality Improvement in Neonatal rEsuscitation (REFINE) study aims to improve the resuscitation skills of health workers using HBB training enhanced with a real-time feedback system (the NeoBeat newborn heart rate meter with the NeoNatalie Live manikin and upright newborn bag-mask with PEEP). The goal is to improve clinical performance and therefore newborn outcomes, monitored and reinforced using a quality improvement process.

## Methods/design

### Aim

The aim of this study is to evaluate the effect of an educational and quality improvement package on intrapartum-related mortality, health workers’ performance in newborn resuscitation, and stakeholder perceptions.

### Study design

This is a pre- and post-intervention observational study. The pre-intervention period July 2017 – September 2018 will be taken as baseline period. The intervention period will be October 2018 – December 2020.

### Study setting

The study will be conducted in the delivery unit at Pokhara Academy of Health Sciences (PoAHS), Pokhara. The hospital has 400 beds and 240 health workers. There is a delivery area for normal deliveries and an operation theatre for Caesarean-sections. The total annual delivery rate was 8610 in 2018, the stillbirth rate is 14 per 1000 total births with a neonatal mortality rate of 19 per 1000 live births.

### Study participants

Study participants include health care providers and babies born in the hospitals. All the health care providers working in the labour room are eligible to the study. During the orientation to the health care providers on the quality improvement project, a group consent will be taken on the observation of health care provider’s simulated practice in neonatalie live and clinical practice. Women with gestational age equal to or more than 22 weeks with a fetal heart sound admitted in the labour room for delivery will be approached for enrollment in the study. Women who consent to get enrolled will be included in the study.

### Data collection

A team of data collectors, supervised by a research manager, will collect information on mortality outcomes and health worker’s performance. The data collectors will extract information from the hospital records on socio-demographic characteristics of women enrolled and observe clinical resuscitation and immediate newborn practices. A standardized data collection protocol will be used to ensure consistency. Training will be provided to the data collectors on selection criteria, obtaining consent, clinical observation and data retrieval.

### Data retrieval

Data will be extracted from the patient records and ward registers for the full study period.

### Clinical observations

Clinical observations will be conducted to capture the clinical variables related to newborn resuscitation. A tablet-based observation tool has been developed and validated by Laerdal Global Health together with researchers from University of North Carolina and Kampala University. This novel application records newborn heart rate together with clinical variables.

### Process evaluation

A qualitative data collection process will be implemented where an independent team will conduct in-depth interviews and focus groups discussions with the health workers and relevant stakeholders (supplementary file 1). Furthermore, video filming will also be done in the end to document the implementation process and outputs.

### Outcome measure

#### Primary outcome measure

Intrapartum stillbirth or death of newborn within 24 h.

#### Secondary outcome measures

Health workers’ performance (based on clinical observations):
◦ Time to apply NeoBeat heart rate meter◦ Time to first spontaneous breath◦ Time of first inflation with bag-mask◦ Ventilation with bag-mask in non-breathing babies at the rate of 40–60 breaths per minute◦ Heart rate from the time of NeoBeat application until 10 min after birth◦ Apgar score at 1, 5 and 10 min after birth◦ Time of first spontaneous breath for non-breathing babies

### Interventions

#### The REFINE intervention package will be implemented using four different approaches

A half a day workshop will be done to review the health worker’s performance on neonatal resuscitation with hospital managers and head of department. The workshop participants will be oriented on the new technology implementation through quality approach;One-day training on Helping Babies Breathe 2.0 version will be provided to health workers working in labour and delivery room;A half of day orientation on the new technologies will be provided to the health workers. Health workers will be oriented on user guidance on neonatalie live, upright bag-mask with PEEP and Newborn Heart Rate Meter. Neonatalie live is a high fidelity simulator which provides real time feedback and debrief on the adequacy and ventilation practice in the simulator. Facilitation will be done to ensure that health workers practice neonatalie live before they resume their work in the labour room on a daily basis. Newborn heart rate meter measures neonatal heart rate and is placed in all babies who require resuscitation at birth. These technologies is co-developed by Laerdal Global Health.A periodic meeting will be facilitated by the research team to discuss on the progress on implementation of the new technologies for improving neonatal resuscitation care using a Plan-Do-Study-Act (PDSA) process. A performance dashboard on neonatal resuscitation will be used to conduct the PDSA meetings (Fig. 1).

**Fig. 1 Fig1:**
[figure not shown]
Intervention model

### Sample size and power calculation

Power calculation for the primary outcome is based on preliminary estimates of an intrapartum mortality of 20/1000 births and 8610 deliveries in the study hospitals per year. We estimate 20% reduction in the intrapartum mortality following implementation of the quality improvement package. With level of significance at 5% and statistical power at 80% to detect 20% reduction in intrapartum mortality we will require 10,023 birth. Intrapartum mortality is calculated as intrapartum stillbirth and first day mortality. Based on the current annual delivery rate, the duration of the intervention period will be 15 months.

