### Data analysis

Analysis of the intervention package effectiveness will be based on comparison between the baseline and end line intrapartum mortality and health worker performance (Fig. 2). Cross-sectional data gathered through the established surveillance system and clinical observations will produce a large dataset allowing for epidemiological analyses. The final report of this protocol will follow the general STrengthening the Reporting of OBservational studies in Epidemiology (STROBE) Statement and figure (supplementary file 2) [12]. Process evaluation will follow Medical Research Council (MRC) framework [13] for implementation and process level data. We have filled Standard Protocol Items: Recommendations for Interventional Trials (SPIRIT) checklist required for study protocol (supplementary file 3).

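### The 10,023 births do not give 80% power for a 20% fall from 20/1000: the protocol's own inputs need about 17,341 per period two-sided, and 10,023 per period gives about 57%.

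*Protocol article*

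**What the plan says.** All the core inputs stand in the protocol article under Sample size and power calculation. The section starts from "preliminary estimates of an intrapartum mortality of 20/1000 births and 8610 deliveries in the study hospitals per year". It then sets the effect: "We estimate 20% reduction in the intrapartum mortality following implementation of the quality improvement package". It concludes: "With level of significance at 5% and statistical power at 80% to detect 20% reduction in intrapartum mortality we will require 10,023 birth". From this it moves to the calendar: "Based on the current annual delivery rate, the duration of the intervention period will be 15 months".

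The section does not say whether the test is one- or two-sided, whether 10,023 is per period or in total, which formula was used, or whether losses were allowed for.

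Two other sections bear on the figure. Data analysis fixes the comparison: "Analysis of the intervention package effectiveness will be based on comparison between the baseline and end line intrapartum mortality and health worker performance". Study design dates the two periods: "The pre-intervention period July 2017 – September 2018 will be taken as baseline period", which is 15 months, and "The intervention period will be October 2018 – December 2020", which is 27 months rather than 15.

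**The concern.** A 20% relative reduction from a 2% event rate is an absolute difference of 4 per 1000. Detecting that between two observed periods takes well over 10,000 births in each, so 10,023 looked too small whether read per period or as a total.

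This is the only power statement for the primary outcome. If it is wrong, the study has a materially higher chance of missing the effect it was designed to find than readers are told. A non-significant result could then be taken as evidence against a 20% benefit when the design was never able to exclude one. The Discussion ties scale-up to evidence of improved outcomes, so a false negative would have consequences.

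**Working it through.** **Inputs.** From Sample size and power calculation: p1 = 0.020; p2 = 0.8 × 0.020 = 0.016; difference 0.004; mean rate 0.018; significance 5%; power 80%; 8610 births per year. From Data analysis: two observed periods. From Study design: 15 and 27 months. Two-sided testing is my assumption, as the usual default; one-sided results are given alongside.

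**Required number, equal periods, pooled variance**

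n = [z_α·√(2 × 0.018 × 0.982) + z_β·√(0.020 × 0.980 + 0.016 × 0.984)]² / 0.004²

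- Two-sided: [1.96 × 0.18802 + 0.8416 × 0.18800]² / 0.000016 = (0.3685 + 0.1582)² / 0.000016 = **17,341 per period**, 34,682 in total. At 8610 a year this is 17,341 / 8610 × 12 ≈ 24 months per period.
- One-sided (z_α = 1.645): **13,660 per period**, 27,320 in total.

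**Can another formula give 10,023?** Two-sided, per period:

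| Method | n |
|---|---|
| Unpooled variance | 17,338 |
| Arcsine | 17,289 |
| Log risk ratio | 17,418 |
| Poisson rates | 17,660 |
| Continuity-corrected | 17,838 |

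All lie more than 70% above 10,023, so the choice of formula does not explain the gap.

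Two routes come close, and each needs inputs that the protocol does not state:

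- *Baseline treated as known.* [1.96·√(0.020 × 0.980) + 0.8416·√(0.016 × 0.984)]² / 0.000016 = 9,025. An assumed 10% loss gives 9,025 / 0.9 ≈ 10,028. No loss allowance is stated, and a fixed baseline is not the comparison in Data analysis.
- *One-sided, with a second period twice as large.* This gives 10,121 in the smaller period. Neither feature is stated, and the sample size section's 15 months against a 15-month baseline is 1:1. The 27:15 ratio from Study design, one-sided, gives 10,515 in the smaller period.

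**Power for 20 versus 16 per 1000**

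Power = Φ{[0.004 − z_α·√(p̄(1−p̄)(1/n1 + 1/n2))] / √(p1(1−p1)/n1 + p2(1−p2)/n2)}, where p̄ is the rate pooled over both periods.

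For 10,023 per period, two-sided: (0.004 − 1.96 × 0.001878) / 0.001878 ≈ 0.170, and Φ(0.170) = 0.567.

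Births by calendar: 8610 × 15/12 ≈ 10,762 and 8610 × 27/12 ≈ 19,372.

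| Births, baseline / intervention | Power, two-sided | Power, one-sided | Reduction detectable with 80% power, two-sided |
|---|---|---|---|
| 10,023 / 10,023 | 56.7% | 68.6% | 26% |
| 10,023 in total, split equally | 32.5% | 44.5% | 36% |
| 10,762 / 10,762 (15 and 15 months) | 59.8% | 71.3% | 25% |
| 10,762 / 19,372 (15 and 27 months) | 71.4% | 80.8% | 22% |

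**Link to the calendar.** 10,023 / 8610 × 12 = 14.0 months. The stated 15 months is therefore close to what 10,023 births implies but not exactly that; the protocol does not explain the extra month.

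**The case against.** The strongest reply is that the protocol does not fix sidedness. With a one-sided 5% test, the 15- and 27-month windows in Study design and full enrolment, power is 80.8%. On that reading the study does reach 80%, so it is too absolute to say that it cannot.

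That holds as far as it goes, but it does not rescue the stated figure. It needs a one-sided test that appears nowhere, and about 19,372 intervention births over 27 months, not the 10,023 births and 15 months in the sample size section. If the fixed-baseline route is where 10,023 came from, the number ignores the sampling error of the baseline rate, which is the error at issue.

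Two qualifications stand. First, the chance of missing a true 20% fall depends on the calendar: about four in ten with 10,023 or 15 months per period, about three in ten with the dated windows (two-sided). Second, the calendar-based powers are best cases. Study participants limits enrolment to consenting women at 22 weeks or more with a fetal heart sound, so fewer births than deliveries will be analysed. It is also fair to say that a confidence interval in the final report would show the imprecision; that limits the harm but does not make the power claim correct.

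**Conclusion.** The concern holds. On any equal-period two-sample reading, 10,023 births do not give 80% power for a 20% reduction from 20/1000. The requirement is 17,341 per period two-sided, about 1.7 times the stated number (17,341 / 10,023 = 1.73), and 13,660 one-sided. Two-sided power is about 57% if 10,023 is per period and about 32% if it is the total. Even the longest calendar in the protocol gives about 71% two-sided.

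The figures assume independent births, a baseline rate of 20/1000 among eligible births, and no background trend in mortality; those based on the calendar also assume that all deliveries are enrolled. A lower rate would reduce power further. As an illustration only, since the protocol gives no such rate for this outcome, 15/1000 with the dated windows gives about 59%.

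**What to change.** Correct Sample size and power calculation as follows:

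1. State whether the test is one- or two-sided, which formula was used, and whether the number of births is per period or in total.
2. Reconcile the 15-month intervention period in this section with the October 2018 to December 2020 window in Study design, and use one of them throughout.
3. Replace the claim of 80% power from 10,023 births with what the chosen calendar delivers. Two-sided, the dated windows give about 71% power for a 20% reduction, or 80% for a 22% reduction. Two 15-month periods give about 60% for 20%, or 80% for 25%. Present these as upper limits that assume full enrolment.
4. Recompute with the event rate and number of births actually observed among eligible births in the baseline period.

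The cost is a change of wording in one section and agreement on one set of dates. No additional births, data items or analyses are required; the stated power becomes less favourable.

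### The intervention period is dated as 27 months in one section and given as 15 months in another, so the post-intervention window of the primary comparison is contradictory

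*Protocol article*

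**What the plan says.** Three sections of the Protocol article bear on the comparison window.

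- **Study design** dates both periods. For the baseline: "The pre-intervention period July 2017 – September 2018 will be taken as baseline period". For the intervention: "The intervention period will be October 2018 – December 2020".
- **Sample size and power calculation** starts from "preliminary estimates of an intrapartum mortality of 20/1000 births and 8610 deliveries in the study hospitals per year", assumes a 20% reduction at 5% significance and 80% power, and concludes that "to detect 20% reduction in intrapartum mortality we will require 10,023 birth". It then derives a duration: "Based on the current annual delivery rate, the duration of the intervention period will be 15 months".
- **Data analysis** rests effectiveness on a "comparison between the baseline and end line intrapartum mortality" and on health worker performance, and that sentence cites Fig. 2, the SPIRIT timeline. The text gives no dates for *end line*. Fig. 2 is not shown in the copy at hand.

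No section separates a roll-out phase from an evaluation phase, or limits the primary comparison to part of the dated intervention period.

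**The concern.** The two durations differ by 12 months, which neither rounding nor inclusive counting of months can explain. Nor is 15 plainly a slip for 27. It follows approximately from the plan's own birth requirement, and it equals the length of the baseline. A reader could therefore defend either 15 months against 15 months or 15 months against 27 months.

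The choice decides which births enter the primary test and hence the precision of the estimate. It also matters for bias. In a before-after study without a concurrent control, a longer post period lets more calendar-time change into the effect estimate. The Discussion itself warns that previous and ongoing quality improvement work may have improved outcomes. If the conflict is still open when mortality by period becomes known, the final choice of window cannot be shown to be independent of the results.

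**Working it through.** **Inputs.** Period dates (Study design); 8610 deliveries per year (Study setting; Sample size); 20 per 1000 at baseline, a 20% reduction, 5% significance, 80% power and 10,023 births (Sample size).

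*Assumptions:* the 20% is relative, so 2.0% falls to 1.6%; every delivery is enrolled; one birth is counted per delivery; the test is two-sided. The article does not state sidedness.

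**1. The plan's own duration.** Monthly deliveries = 8610 / 12 = 717.5. Months needed = 10,023 / 717.5 = 13.97. A 15-month period gives 717.5 × 15 = 10,762.5 births, about 7% more than required. The stated 15 months is therefore reproduced as a rounded-up figure.

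**2. Durations by date, counted inclusively.**
- July 2017 to September 2018: 15 months.
- October 2018 to December 2020: 27 months.
- October 2018 to December 2019: 15 months.

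**3. Births in the post period.**
- 15 months: about 10,762.
- 27 months: 717.5 × 27 = 19,372.5, about 19,372.
- Ratio: 27 / 15 = 1.8.

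**4. Power under each window.** With baseline size n1 = 10,762.5, post-period size n2, p1 = 0.020, p2 = 0.016 and pooled proportion p̄:

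Power = Φ[(0.004 − 1.96 × SE0) / SE1], where SE0 = √[p̄(1 − p̄)(1/n1 + 1/n2)] and SE1 = √[p1(1 − p1)/n1 + p2(1 − p2)/n2].

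| Post period | n2 | p̄ | SE0 | SE1 | z | Power |
|---|---|---|---|---|---|---|
| 15 months | 10,762.5 | 0.01800 | 0.001812 | 0.001812 | 0.247 | 59.8% |
| 27 months | 19,372.5 | 0.01743 | 0.001573 | 0.001623 | 0.565 | 71.4% |

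Read as one-sided, the same calculation gives about 71% and 81%.

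**5. What the two windows share (illustration only).** Both tests use the same baseline, and the first 15 months lie inside the 27. Under no effect, the correlation of the two z statistics is √[(1/15 + 1/27) / (1/15 + 1/15)] = √0.778 = 0.88. If both windows were tested at two-sided 5% and a significant result from either were reported, the chance of at least one false positive in either direction would be about 7.2%.

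**The case against.** The strongest reply has four parts.

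- **The window may be defined elsewhere.** The sentence that uses *end line* cites the timeline figure, and a full protocol or analysis plan may give dates. This stands. A reader might infer that *end line* has no definition at all, but with Fig. 2 not shown that is not established. The two-period design also makes the whole intervention period a natural reading. Neither the figure nor an analysis plan, however, removes the conflict between two current statements in this article.
- **Nothing suggests that a window will be picked on results.** This also stands. A reader might infer from the dashboard used in the Plan-Do-Study-Act meetings that the team watches the primary outcome accumulate. The Interventions section describes a dashboard of resuscitation performance and does not say that it shows mortality. Nor does any section name a late evaluation window. The 7.2% shows what an unresolved choice could cost; it is not a description of planned conduct.
- **The shortfall in power is mainly a separate matter.** Largely true. A standard two-sided calculation for 2.0% against 1.6% needs about 17,341 births per period, so 10,023 is too few under either duration. The gap between 60% and 71% nevertheless comes from the window alone.
- **With a one-sided test, 27 months reaches 81%.** True, but the article does not state a one-sided test, and its sample size section uses 15 months, which would give about 71%.

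**Conclusion.** The article is wrong as written in one of two places: the intervention period cannot be both 27 and 15 months. The contradiction follows from the text alone and needs no assumption. Its size is 12 months, or about 8,610 post-period births.

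The power figures of about 60% and 71% rest on full enrolment, a two-sided test and a relative 20% reduction. Losses to consent or eligibility would lower both.

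The documents do not show which duration is the intended one. Fifteen months fits the 10,023 births and the baseline length. Twenty-seven months is what the dates say and gives more power, but it admits more calendar-time change. What matters is that one window is fixed in advance. Because the conflict concerns the primary comparison and is cheap to remove, it should be resolved before the analysis.

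**What to change.** 1. Reconcile Study design with Sample size and power calculation so that both give one intervention period with start and end dates. Fix it before mortality by period is examined, and record when this was done.
2. In Data analysis, state that *end line* means all eligible births in that period, and check that Fig. 2 agrees.
3. Restate expected births and power for the chosen window against the 15-month baseline, and state whether the test is one- or two-sided.
4. Label an analysis of any other window as supportive.
5. If the 27-month period is kept, acknowledge the greater exposure to calendar-time change. If 15 months is kept, correct the dates.

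The cost is wording changes in three sections and a stated power that, for a two-sided test, is likely to be less favourable than 80%. Whether data collection is affected depends on the choice, because the length of the full study period is itself what is in dispute.
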